## Abstract

Stroke is a highly disabling condition, for which music therapy is regularly used in rehabilitation. One possible mechanism for the effects of music therapy is the motivational aspect of music, for example regarding treatment adherence based on improved mood. In this study, changes in motivation related to Neurologic Music Therapy (NMT) techniques during rehabilitation in the subacute phase after stroke will be investigated. Using a randomised within-subjects cross-over design, the effects of two NMT techniques and related motivational indices will be investigated. Data will be collected at three timepoints: baseline (TP1), after being randomised into groups and receiving NMT or standard care (TP2), and then at a third time point after the cross-over and having received both conditions (TP3). This design allows to counteract order effects, time effects due to spontaneous and/or nonlinear recovery, as well as single-subject comparisons in a relatively heterogeneous sample. Twenty adult participants who have experienced a supratentorial ischaemic or haemorrhagic stroke and are experiencing upper-limb impairments and/or cognitive deficits will be included. Behavioural measures of motor function, cognition, and quality of life will be collected, along with self-reported indices of overall motivation. The study outcomes will have implications for the understanding of the underlying mechanisms of music therapy in stroke recovery, more specifically regarding the relevance of motivational states in neurorehabilitation.

## Introduction

1

Music-based interventions have been used successfully in the treatment of impairments after stroke and have been shown to improve various functions, such as gait [1], speech/language [2], impaired arm motor function [[3], [4]], and attention [5]. Possible underlying mechanisms have been described as focusing on increased repetition, potentially improved temporal skills, motivation, and multisensory embedding of movement [[6], [7]]. Despite these aspects of music being commonly used by music therapists in their daily clinical practice [8] and Music Therapy being regularly offered as part of a rehabilitation program, there remains a gap in the scientific evidence to support these methods, and the empirical support for its underlying mechanisms. Specifically, motivational aspects of music, arguably due to improved mood and emotion regulation affecting the drive to improve, have been found to affect clinical and nonclinical outcomes in a systematic review [9]. In the current paper, we conceptualise motivation as the drive to participate in therapy and self-regulate emotions. We also focus on techniques drawn from Neurologic Music Therapy (NMT), a clinical system of music interventions based on the neuroscience of music perception, cognition, and production and how music can influence and change non-musical brain and behaviour function.

Neurological and functional recovery (e.g. movement, cognition and/or independent living) primarily occurs in the acute and sub-acute phase [10], and only 5–20 % of patients ever fully recover in terms of their upper-limb function [11], including arm and hand movements. Cognitive deficits occur in more than half of stroke survivors, with attentional deficits as the most prominent. Attention is linked to motor recovery, as it is considered essential for motor learning [12]. The interaction between movement and cognition is commonly seen in people who have experienced a stroke through combined presentation of symptoms and related recovery. For instance, the level of sustained attention at two months post-stroke was found to predict motor recovery two years later [13], and music-based interventions have shown potential to improve both domains (e.g. Refs. [[14], [15]]).

In the field of neurorehabilitation, motivation has been demonstrated to be a link between cognition and motor performance, playing an important role in rehabilitation outcome determining factors [16]. Motivation is therefore considered to be a mechanism for functional improvements (e.g. Ref. [13]), including in music therapy, likely due to potential mood improvements [14], but it has not been explicitly investigated [9]. Moreover, in previous research, motivational differences have anecdotally been viewed as confounders, rather than an important aspect of the therapeutic process that may also affect elements of a patient's functional level. The motivational potential of music is well-established in athletics [17], while the effect of music on motivation is more often formulated in terms of mood, which is more generally extensively investigated and utilised in clinical settings to regulate stress and anxiety (e.g. Ref. [18]). Physiological correlates of stress reduction with music more generally are increasingly elucidated [19] with potential for application in many other settings. In further support of the role of motivation in music-based intervention methods, studies have also found that movement rehabilitation utilising music may be more effective than those without an auditory component [1,20] with evidence supporting improvements in motor function, mood, and cognition of patients [21]. Interestingly, personality traits, such as agreeableness, extroversion, openness, neuroticism and conscientiousness, have been linked to not only music-based movement [22] and musical emotion regulation [23], but also well-being measures during stroke recovery, including quality of life [24], and mood [25]. While possibilities for quantifying motivational states are still in the early stages, validated measures have been developed focusing specifically on motivation for rehabilitation in stroke [26].

In the current study, we aim to assess variations in the intrinsic motivation to engage in musical activities over three timepoints: at baseline (TP1), after either the intervention or control condition (TP2), and after the other condition (TP3) in a cross-over design. Studies in patients with mood disorders have shown that engaging in music therapy was associated with adherence to other therapeutic interventions, such as physical therapy or occupational therapy [27,28]. While this has not been demonstrated in stroke patients, we seek to examine if music therapy is associated with higher attendance to other therapies. Research examining both intrinsic and extrinsic motivation has focused on music-reward in wanting versus liking paradigms [29], as an indication of motivation [30,31], but this has not been examined in stroke patients undergoing music therapy, for whom motivation is thought to underlie functional recovery [32].

The main aim of this project is to investigate within-subject changes in motivation during two NMT interventions. Secondly, we aim to assess the direct effects of the two NMT interventions on motoric and cognitive functional outcomes (in particular upper limb function and attention/concentration) and subjective well-being, as compared to a within-subject control period consisting of usual (or standard) care. Here, several caveats should be taken into account, that stem from not having an active control condition that would assess NMT-specific motivational effects rather than the effect of adding additional NMT to standard care. While there are aspects of usual care that preclude standardisation (see also [33]), more recent guidelines indicate that its content should primarily be driven by the trial's requirements to protect participants, inform practice, and be methodologically robust, efficient, feasible and acceptable to stakeholders [34]. Based on exchanges with the care facility and its multidisciplinary team, a standard care control period was deemed most pragmatic, as well as fitting for the target group and clinical context.

We hypothesise that NMT techniques targeting motor and cognitive outcomes will lead to increased self-reported overall motivation as compared to a period of no treatment. Secondly, we expect that changes in motivation will correlate with changes in functional outcomes in motor, cognitive, and mood domains. In terms of effectiveness, we expect the NMT interventions to positively affect functional outcomes within each participant. Finally, the study also aims to explore whether changes in motivation predict self-reported ratings of well-being, and whether participating in NMT increases adherence to other rehabilitation therapies. As a secondary aim, the effectiveness of the two NMT interventions will be assessed by comparing it to our care-as-usual waiting period. Here, we expect clinical outcomes of motor and cognitive function to improve more with additional NMT than without, controlling for the post-incident recovery time.

## Protocol

2

### Objectives

2.1

The primary objective is to investigate increases in motivation as a hypothesised mechanism underlying the effectiveness of two NMT interventions for stroke patients experiencing upper-limb impairments and/or cognitive deficits. The secondary objective is to assess the within-subject effects of the NMT interventions as compared to the control period on behavioural outcomes of motor functions, cognitive functions, and self-reported measures of well-being.

### Study design

2.2

The study will employ a within-subject cross-over design; as stroke patients are not a homogenous group, this design is adopted to control for expected within-subject variation. To account for variability in brain damage that is caused by stroke, each subject thus serves as their own control. The cross-over design will account for order effects, as participants will be randomised into either receiving the intervention or the control phase first (AB), and vice versa (BA), while also allowing for the assessment of the intervention effectiveness (as part of the secondary goal).

All subjects will receive two NMT techniques targeting both upper-limb movement and attention. The study aims for participants to receive 9 sessions of NMT over 3–6 weeks, however, participants who complete a minimum of 6 sessions will be included in the primary analysis. The frequency of clinical contacts will aim for an average of 2–3 sessions per week but will be adjusted to a patient's expected length of stay and ability, using a tailored approach. Dosage will depend on a participant's rehabilitation trajectory, as subacute patients generally are admitted for a minimum of ±6 and a maximum of 16 weeks.

Fig. 1 gives an overview of the design and procedures that the subjects will undergo within the course of the research, based on a rehabilitation trajectory of 8–10 weeks. When participants’ rehabilitation trajectory is shorter (6–8 weeks) or longer (12–16 weeks), then the intervals between baseline, mid-trial and final measures are adjusted accordingly.

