#### Exclusion criteria

2.3.3

Participants will be excluded if this is not their first stroke or if a second stroke occurs during their stay at the rehabilitation centre. Further exclusion criteria are the following: i) upper limb paralysis as assessed by a score <2 points on the Medical Research Scale (MRC) for muscle strength [40]; ii) severe behavioural and/or cognitive problems preventing understanding or carrying out instructions or risk of dementia (a score <21 on the Mini-mental state examination; MMSE; [41]); iii) severe communication problems, e.g., severe aphasia and/or apraxia of speech; iv) known psychiatric, substance abuse, or neurological comorbidity. For participants who score <24 on the MMSE, a follow-up check will be carried out for a possible dementia diagnosis which would retrospectively lead to exclusion. Fig. 2 illustrates the criteria for inclusion and exclusion for this study.

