#### Study procedures

2.5.3

The protocol for this study has been approved by the Medical Research Ethics Committee of Leiden University/University of the Hague/Delft University, protocol number: NL78853.058.22. The study registered under ClinicalTrials.gov identifier: NCT06291480, with preregistered hypotheses at the Open Science Framework (https://osf.io/dzq7b).

Participants will be recruited ideally within the first three days after being admitted to the Leo Polak Rehabilitation Centre in Amsterdam, after review of the referral and handover from the main hospital. Patients will be first approached by a practitioner not involved in the study, who will inform the patient about the research study and provide the recruitment materials. If the patient indicates interest, the researcher will provide the patient with more information and the participant information letter, and if they wish to participate, they will be asked to sign the informed consent form.

An assessor will administer a checklist of exclusion/inclusion criteria to screen patients eligible to enrol in the study. Clinical measures administered at screening will be the Mini Mental State Examination (screening for cognitive impairment) (MMSE [41]), the National Institute of Health Stroke Scale (stroke severity) (NIHSS; [56]), and the Medical Research Council Scale for muscle strength (severity paresis arm/hand) (MRC-muscle strength [40]. All team members performing this screening are NIHSS-certified (Ortiz & Sacco, 2007). Additional medical information, such as type of stroke, location, lesion type etc, will be extracted from the client's medical dossier and triage process.

The intervention condition will consist of a target of 9 sessions in total, administered over an average of 5 weeks, but may span from 2 to 8 weeks according to the patient's length of stay at the Leo Polak Stroke Rehabilitation Centre. All music therapy interventions will be delivered by a registered/board certified/licenced music therapist who has had advanced training in NMT.

The protocol aims for participants to receive a minimum of two sessions per week over the duration of the study enrolment. However, this schedule may not be possible in every case due to the participants’ length of stay. Participants who complete a minimum of 6 sessions will be included in the final analyses. The number of sessions each participant receives will be recorded and treated as a variable in the statistical analysis.

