### Statistical analysis

2.6

Descriptive statistics for all relevant variables, such as changes in motivation, upper limb function and/or attention/concentration skills, will be calculated (means, standard deviations, etc.). Assumptions of all statistical analyses will be checked, and appropriate measures will be taken in case of violations (e.g., transformations, nonparametric testing, or bootstrapping). Effect sizes will be calculated for each effect (e.g., Cohen's *d*). Statistical tests will be performed with an alpha level of p ≤ .05 to determine statistical significance of results. Because of the randomised design, possible bias introduced by missing data will be controlled for using an intention-to-treat (ITT) analysis performed on all subjects who complete the baseline measurements, to assess whether data is missing randomly. If so, these may be completed with imputed data. Given the relatively small sample size of the study, this allows for a per-protocol analysis to also be conducted on datasets with missing data points, and the results from the ITT analysis will be verified on subjects who completed the entire study protocol, including all measurements (e.g. Ref. [57]). If needed, data analysis procedures with more robustness for missing data will be utilised (i.e., multilevel models). The self-reported motivation for sessions attended for other interventions offered at the rehabilitation centre will be recorded and compared between subjects as well as between sequences (AB/BA). Carry-over effects due to the cross-over design will be assessed by examining a treatment-by-period interaction. A significant difference between the two intervention or control phases of the AB/BA sequence, will result in significant treatment-by-period interaction indicating a carry-over effect (Lim & In, 2021). In case a significant carry-over effect is found, we will control for this in the analysis.

Other aspects that may be used as covariates in post-hoc analyses to interpret results at the group level are individual differences in diagnostic intake measures, age, and qualitative clinical observations or situations that may affect motivational states.

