The primary analysis concerns the change in motivation scores (BMQ-S) between the control and intervention period, controlling for the order of conditions. Additionally, a correlation between changes in motivation with changes in functional outcome measures (motor, cognition, mood) will be calculated. For our secondary analysis, changes in functional measures will be compared between control and intervention periods to assess effectiveness of NMT. As exploratory analyses, correlations between functional improvements and possible predictors such as musical engagement, optimism, personality traits and expectations of NMT will be calculated. Finally, self-reported motivation for other rehabilitation specialisms will be compared between the intervention and control period. Participants will be included if they have completed at least 6 sessions of Music Therapy.

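### The primary analysis set is defined in two incompatible ways, and the version based on at least 6 NMT sessions selects patients after randomisation on something partly tied to the outcome construct

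*Protocol article*

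**What the plan says.** Three places define the analysed set by treatment received:

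- Section 2.2, Study design, after setting a target of 9 sessions: "participants who complete a minimum of 6 sessions will be included in the primary analysis".
- Section 2.5.3, Study procedures: "Participants who complete a minimum of 6 sessions will be included in the final analyses".
- Section 2.6, Statistical analysis, in the paragraph that defines the primary BMQ-S comparison: "Participants will be included if they have completed at least 6 sessions of Music Therapy".

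Elsewhere section 2.6 defines a different set. Bias from missing data is to be controlled "using an intention-to-treat (ITT) analysis performed on all subjects who complete the baseline measurements, to assess whether data is missing randomly", with imputation possible if the answer is favourable. It then adds that "the results from the ITT analysis will be verified on subjects who completed the entire study protocol, including all measurements".

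On session count, section 2.5.3 also states: "The number of sessions each participant receives will be recorded and treated as a variable in the statistical analysis".

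**The concern.** A 6-session minimum and an ITT set of everyone with baseline data are different populations. Two analysts who each follow the article faithfully could report different primary results. The trial has about 20 patients, a self-reported primary outcome and no blinding of researchers or assessors (2.5.2), so the choice should not stay open until data are seen.

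The session rule is also the weaker choice. Whether a patient reaches 6 sessions is known only after randomisation. The Introduction defines motivation partly as a person's drive to take part in therapy, so a cut on therapy sessions completed is in part a cut on the construct being measured. Only NMT sessions count, so the rule may also bite differently in the two sequences: a patient with NMT first can satisfy it in period 1, while a patient with NMT second who leaves early cannot.

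**Working it through.** **1. The texts side by side**

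| Place | Who is analysed | Role |
|---|---|---|
| 2.2 | at least 6 NMT sessions | primary analysis |
| 2.5.3 | at least 6 NMT sessions | final analyses |
| 2.6, primary analysis paragraph | at least 6 NMT sessions | condition of inclusion |
| 2.6, missing data | all with baseline measurements | ITT |
| 2.6, missing data | entire protocol and all measurements | verifies the ITT result |

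Read alone, 2.2 could merely tolerate fewer than 9 sessions. The sentence in 2.6 makes 6 sessions a condition of inclusion. A result that is verified on completers is naturally the lead result, yet 2.2 gives the primary label to the session-based set. There are also two completer definitions (at least 6 sessions; entire protocol), which need not coincide.

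**2. How many patients could differ**

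Inputs from 2.3.1: 18 needed (alpha 0.05, power 0.8, correlation 0.56), attrition or missing data 10–20%, recruitment until 20 have completed.

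- The plan's 18 reproduces with an exact one-sided test of a correlation (17 patients give 79.2% power, 18 give 81.4%). The conflict over the analysis set does not depend on this figure.
- Randomised patients needed for 20 completers: 20/0.9 = 22.2, so 23; 20/0.8 = 25.
- Difference between the sets: 23 − 20 = 3 to 25 − 20 = 5 patients.

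This treats all attrition as falling below 6 sessions. The article does not say so, so 3–5 indicates scale only.

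**3. Illustration of the possible shift**

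The documents give neither a BMQ-S standard deviation nor an expected share of patients below 6 sessions, so the following rests on assumptions. Let the individual NMT-minus-control improvement be standard normal, let r be its correlation with a latent attendance variable, and exclude the lowest fraction p on attendance. The mean among those kept shifts by

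shift = r × φ(z_p) / (1 − p)

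- p = 0.10: φ(1.282)/0.9 = 0.1755/0.9 = 0.195. At r = 0.3 the shift is 0.058; at r = 0.5 it is 0.097.
- p = 0.20: φ(0.842)/0.8 = 0.2800/0.8 = 0.350. At r = 0.3 the shift is 0.105; at r = 0.5 it is 0.175 (0.17 when cut to two decimals).
- r = 0: the shift is 0.

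Simulation over a wider assumed range (r = 0.2 to 0.6, same p) gave 0.04 to 0.21 SD, and essentially zero at r = 0. A negative r reverses the sign.

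**The case against.** The strongest reply is that this is an unclear hierarchy and little more. Section 2.6 never calls ITT primary, and both ITT and multilevel models are already planned. That is fair as to the effort needed, but the article still fixes the analysed set twice and incompatibly, which is more than detail left to an analysis plan.

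Several stronger readings are tempting, and the documents do not support them:

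- *The rule selects on the primary outcome and biases towards NMT.* Sections 2.2, 2.3.2 and 2.5.3 link session number to length of stay and ability. The outcome is a within-person difference in change, so a stable tendency to attend largely cancels. Early discharge could reflect fast recovery. Attendance is at most a partial proxy, and the direction is unknown.
- *The randomised comparison is lost.* Randomisation concerns order. Excluding a patient removes both periods, so the within-person comparison survives among those kept. Balance between sequences and representativeness can suffer.
- *Early leavers with NMT first are kept while those with NMT second are dropped.* The former meet the rule but have no control-period change, so they give no full contrast unless modelled or imputed. Unequal exclusion is possible, not shown.
- *The 10–20% is the share below 6 sessions.* Section 2.3.1 calls it attrition or missing data. Its cited study lost 4 of 20 in the music arm and 2 of 20 in the conventional arm to withdrawal or exclusion, not to low attendance.
- *Session number is a covariate in the primary model.* Section 2.6 names only order as an adjustment there; 2.5.3 does not say which analysis uses session number.
- *Patients are deleted after a second stroke.* Section 2.3.3 excludes a patient "or if a second stroke occurs during their stay at the rehabilitation centre", but no text says how data before the event are analysed.

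**Conclusion.** The concern holds in this form: the primary analysis set is defined inconsistently, and the session-based definition conditions on a post-randomisation variable that the protocol's own definition of motivation links partly to the outcome construct. The first half rests on the text alone. The second half establishes that bias is possible; its direction and size are not documented. The 0.06–0.17 SD illustration depends on an assumed positive correlation of 0.3–0.5 and an assumed 10–20% excluded, and it vanishes at zero correlation.

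A smaller related fault also stands. An ITT analysis cannot establish whether data are missing at random, yet 2.6 makes imputation depend on that answer.

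**What to change.** Amend sections 2.2, 2.5.3 and 2.6 so that they agree:

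1. Name one primary set: all randomised participants with TP1, analysed in their assigned sequence.
2. Use the multilevel model that 2.6 already holds in reserve, with treatment, period and sequence, on every observed BMQ-S value.
3. Label the set with at least 6 sessions and the complete-protocol set as sensitivity analyses.
4. State that session number is used only in a separate dose-response description within NMT periods.
5. Remove the statement that the ITT analysis shows whether data are missing at random. State missing-at-random as an assumption of the model instead.

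This changes wording only and needs no new visits or measurements. Low-attendance patients may dilute the estimated effect, and the model relies on missing-at-random for absent visits. A patient with TP1 only still contributes no treatment contrast, so the gain is limited to those with at least one later measurement.
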